## **5.7 Data collected and data analyses**

### **5.7.1 Behavioural and self-report data**

In addition to the persistent and repeatedly self-reported masses, immunological parameters and the behavior during the standardized positive interaction at laboratory visit 1 are recorded as described above.

The behavioral and self-report data are evaluated at the Department of Clinical Psychology and Psychotherapy of the Psychological Institute of the University of Zurich (Head: [name]. [name]).

### **5.7.2 Biological data**

The hormonal data (salivary cortisol) and the salivary enzyme alpha amylase will be analyzed in the psychobiological laboratory of the Department of Clinical Psychology and Psychotherapy of the Psychological Institute of the University of Zurich (Head: [name]. [name]).

The following parameters will analyzed as wound healing parameters:

- Size of the wound (photographed with measuring tape immediately after wound application and 7 days after wound application)
- Trans-epidermal Water Loss (TEWL; using an evaporimeter before wound application, immediately after removal of the epidermis, 24 hours after removal of the epidermis, 7 days after removal of the epidermis)
- Epithelialisation (by microscopy before wound application, immediately after removal of the epidermis, 24 hours after removal of the epidermis, 7 days after removal of the epidermis)
- Mediators of wound healing: cytokines in the wound fluid (TNF alpha, IL1, IL6; analysis of the wound fluid 1) from two blisters immediately after application of the suction blisters, 2) from two intact blisters 24 hours after application of the suction blisters).

The evaluation of the data on wound size, TEWL and epithelialization will be carried out in the Dermatology Department of the USZ. The cytokine concentrations are analyzed by the Cytolab laboratory ([name], [name]). All data will be analyzed in strict compliance with the anonymization of the subjects (see below).

### **5.7.3 Statistical data analyses**

The primary endpoint of sub-study 1 is reached when 100 couples have been examined.

The group differences analyzed in sub study 1 (oxytocin vs. placebo, men vs. women) in relation to the main outcome variable wound healing will be evaluated using analyses of variance (ANOVAs). Associations between the repeated measures data of the EMA part of the study and the main outcome variable wound healing will be analyzed using hierarchical linear models (HLM) to account for the dependent data structure between partners.

The significance level of the data analysis is set at 5%. Individual missing data points are replaced by the group-specific mean value. The data of prematurely discontinuing study participants are analyzed for statistically significant differences with the remaining group.

All psychobiological data will only be analyzed after completion and termination of the sub-study in order to minimize inter-assay variance. Self-report and behavioral data will be analyzed in 6-month tranches.

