### *4.1 Background and rationale of the clinical study*

The planned research project aims to answer the question of whether the hypothalamus hormone oxytocin modulates the perception of couple-specific stimuli (such as bonding and sexuality) and couple interaction. The central question to be investigated is whether oxytocin in interaction with couple interaction has an influence on wound healing and thus on individual health. It is assumed that the assumed effect is determined by the perception of couple-specific variables and is therefore specific to the interaction of couples. This specificity is to be tested in a sub-study. The project therefore consists of two parts:

*1) In sub-study 1*, the interaction of oxytocin and couple interaction in the everyday life of couples on the healing of a standardised applied wound is investigated. In a 2x2 design involving 100 couples, the influence of positive couple interaction and oxytocin, or of no instructed interaction and placebo, on wound healing over the course of a week is tested. It is assumed that oxytocin and positive couple interaction have a positive influence on wound healing. It is also assumed that oxytocin and positive couple interaction have a positive influence on the couples' mood in everyday life and reduce everyday stress.

*2) Sub-study 2* of the project will specifically investigate the influence of oxytocin on the perception and evaluation of attachment stimuli and sexual stimuli compared to neutral control stimuli. This study will investigate the interest in the stimuli in 88 people by questioning the test subjects on the one hand and by means of eye tracking on the other.

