#### ***5.4 Study design***

Sub-study 1 will be conducted according to ICH-GCP and in a randomized double-blind design. A total of 4 study arms will be investigated, which differ as follows: Oxytocin + positive couple interaction, oxytocin + no instructed interaction, placebo + positive couple interaction, placebo + no instructed interaction. 25 pairs per study arm will be randomly assigned. The probability of allocation to one of the 4 study arms is 25%, and the probability of allocation to oxytocin or placebo is 50%.

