##### **5.4.1 Research sample & power analysis**

100 heterosexual couples aged 25-45 years will be analyzed. Using G\*Power (Buchner, Faul, & Erdfelder, 1998), a sample size of N=76 was calculated for sub-study 1 with regard to the

main outcome variable "wound size" (see below) (effect  $f = .40$ ; power = .82,  $\alpha = .05$ ).  
The total N is set to  $N=100$  in order to be able to compensate for any dropouts.

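### Section 5.7.3 lists oxytocin and sex but not the randomised couple-interaction factor or its product with oxytocin, and the stated power of .82 does not fit the contrasts it lists

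*Protocol*

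**What the plan says.** All references are to the Protocol, sub-study 1.

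- **Aim (4.1).** "The central question to be investigated is whether oxytocin in interaction with couple interaction has an influence on wound healing". The same section describes the design: "In a 2x2 design involving 100 couples, the influence of positive couple interaction and oxytocin, or of no instructed interaction and placebo, on wound healing". It expects oxytocin and positive couple interaction each to help healing.
- **Design (5.4).** "A total of 4 study arms will be investigated", formed by crossing oxytocin or placebo with positive interaction or no instructed interaction; "25 pairs per study arm will be randomly assigned".
- **Questions and hypotheses (5.1, 5.2).** These are worded as oxytocin against placebo only. Hypothesis I c is that oxytocin speeds wound healing. Everyday interaction appears in 5.2 only as an exploratory mediator, which is not the randomised instruction.
- **Sample size (5.4.1).** "a sample size of N=76 was calculated for sub-study 1", for wound size, with f = .40, power .82 and alpha .05. The total was raised to 100 "in order to be able to compensate for any dropouts". No test is named.
- **Analysis (5.7.3).** "The group differences analyzed in sub study 1 (oxytocin vs. placebo, men vs. women") are to be compared on wound healing by ANOVA. Hierarchical linear models are reserved for associations between the momentary-assessment data and wound healing. The significance level is 5%.

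**The concern.** The list in 5.7.3 includes sex, which is not randomised, and omits instructed interaction, which is. It has no oxytocin × instruction term, although that term is what answers the question in 4.1. The hierarchical models do not fill the gap, because they relate diary-type measurements to healing and do not compare randomised arms.

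Three things are at stake:

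1. Half the couples receive an intervention whose effect on healing, alone or combined with oxytocin, has no planned test.
2. An instruction effect, which 4.1 expects, would remain in the error term of the oxytocin comparison.
3. The reader is given one power figure without knowing which test it describes, and none for the interaction.

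Because the list is explicit, this is more than detail left to an analysis plan. A plan that followed 5.7.3 would omit the second factor, and one that added it would depart from the protocol.

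**Working it through.** **Inputs.** From 5.4.1: f = .40, alpha = .05, N = 76, power .82, total 100. From 5.4: four arms of 25 couples. N is read as couples because it is raised to the 100 couples enrolled.

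**Method.** Fixed-effects ANOVA power from the noncentral F distribution, with λ = f²N and denominator df = N − number of cells.

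**1. Reproducing the stated .82.** λ = .40² × 76 = 12.16.

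| Test at N = 76, f = .40 | df | Power |
|---|---|---|
| Four-arm omnibus | 3, 72 | .823 |
| 3-df effect in eight cells (four arms × sex) | 3, 68 | .822 |
| 1-df main effect or interaction, four cells | 1, 72 | .931 |
| Two-group comparison | 1, 74 | .931 |
| Three-group omnibus | 2, 73 | .874 |
| Eight-cell omnibus | 7, 68 | .664 |

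Only a 3-df effect gives .82. For the four-arm omnibus test, N = 75 gives .818, so 76 is the smallest N that reaches .82. A 1-df test reaches .82 at N = 54.

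**2. Power of the 1-df tests at the protocol's f.** With f = .40 for the term itself, power is .931 at 76 couples and .977 at 100 (λ = .16 × 100 = 16). In a balanced 2×2, an interaction has f = (difference of differences in SD)/4, so f = .40 means 4 × .40 = 1.6 SD.

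**3. Interaction power at smaller effects (assumed range).**

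| Interaction f | Difference of differences | Power, 76 couples | Power, 100 couples |
|---|---|---|---|
| .30 | 1.2 SD | .73 | .84 |
| .25 | 1.0 SD | .58 | .70 |
| .20 | 0.8 SD | .41 | .51 |

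As one illustration, suppose f = .40 is the spread across the four arms and only the combined arm benefits, by δ SD. Then overall f = δ√3/4 = .40, so δ = .92. The interaction has f = δ/4 = .23, and power is .51 at 76 couples and .63 at 100.

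**4. Cost of leaving instruction in the residual.** An omitted instruction effect with f = .40 inflates the error variance by 1 + .40² = 1.16. Oxytocin's f falls from .40 to .40/√1.16 = .371. At 100 couples λ falls from 16 to 13.79, and power from .977 to .957. For a smaller oxytocin effect the loss is larger: with an assumed f = .283, power falls from .80 to .74.

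**The case against.** The strongest reply is that the operative sections agree with one another: 5.1 and 5.2 ask about oxytocin against placebo, and 5.7.3 tests exactly that. The central-question wording comes from the background section, which expects two positive influences and does not predict synergy. This stands in part. A reader might infer that the trial never tests its main hypothesis; the documents do not support that, because hypothesis I c is tested. What remains is a conflict between 4.1 and 5.4 on one side and 5.1, 5.2 and 5.7.3 on the other.

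A second reply is that the bracketed list is shorthand. Section 6.6.2 uses the same style and omits picture category, although the sub-study 2 hypothesis turns on it. The parallel is partial, since picture category is a within-subject factor and the list in 5.7.3 concerns groups. Model terms may be left to an analysis plan, but a list of group factors that omits a randomised one still needs correcting.

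A reader might also conclude that the sample is too small. The protocol's own inputs do not show that: at f = .40 the 1-df oxytocin test has more power than stated. The .51 and .63 rest on an assumed pattern in which only one arm benefits, which is not the expectation in 4.1. With equal allocation, omitting instruction does not bias the oxytocin estimate.

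Finally, 5.4.1 names no test, and two different 3-df layouts round to .82. Attributing the figure to a four-arm comparison is therefore an inference, though a 1-df test is ruled out at the stated inputs.

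**Conclusion.** The point holds, and should be fixed. Section 5.7.3 omits the second randomised factor and the oxytocin × instruction term, so the question in 4.1 has no planned test. The oxytocin main effect is tested and, at f = .40, has power of about .93 at 76 couples and .98 at 100 if instruction is in the model or has no effect. Leaving out an instruction effect of f = .40 costs about two percentage points at 100 couples (.977 to .957), and more if the oxytocin effect is smaller.

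The stated .82 is consistent with a 3-df comparison of the four arms and not with the 1-df contrasts listed. No power is stated for the interaction, where f = .40 would require a 1.6 SD difference of differences. These figures assume that N counts couples, with one outcome value per couple and equal arms.

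**What to change.** - **5.7.3:** fit oxytocin, instruction and oxytocin × instruction as between-couple factors, with sex within couple. Test in fixed order, each at 5%: the oxytocin main effect (hypothesis I c), then the 1-df oxytocin × instruction term (the 4.1 question), then the instruction main effect.
- **5.2:** add hypotheses for the interaction and for instruction.
- **5.4.1:** name the test to which .82 belongs. State power for the 1-df tests at 76 and 100 couples: .93 and .98 if the term itself has f = .40, noting that for the interaction this is a 1.6 SD difference of differences. Add at least one smaller interaction effect, such as the assumed case above (.51 and .63 at f = .23), labelled as an assumption.

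**Cost.** Wording only. Both factors are already randomised, and no change to data collection or sample size is needed. The drawback is that the stated power for the interaction may look less favourable than .82.

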| Clinical phase:                           | Clinical study phase                                                                                                                                                                                                                                                       |
| Study design:                             | Double-blind, randomised, placebo-controlled                                                                                                                                                                                                                               |
| Duration of study:                        | Sub-study 1: 1 week, Sub-study 2: 1 or 2 x approx. 2h                                                                                                                                                                                                                      |
| Study centres                             | Monocentric                                                                                                                                                                                                                                                                |
| Investigator(s):                          | [name], [name] [name], [name], [name]                                                                                                                                                                                                  |
| Aims and objectives of the clinical trial | Sub-study 1: Wound healing after one week, recorded via transepidermal water loss (TEWL), wound size and epithelialisation of the wound
Sub-study 2: Interest in the images presented, recorded using gaze duration, gaze focus and subjective evaluation of the images |
| Number of subjects:                       | Sub-study 1: 200 (100 pairs)
Sub-study 2: 88                                                                                                                                                                                                                            |

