**Suction bubble application**

If there are no objections to the subjects' participation, all inclusion criteria are met and there are no exclusion criteria, they are asked how they feel. A doctoral student in dermatology then applies standardized suction blister wounds to the forearm under the supervision of the investigator [name] [name] (both partners receive the suction blisters). During this procedure, the couples are informed about the second laboratory appointment, the momentary assessment part of the study, and the positive/negative couple interaction. Mood and pain perception are repeatedly recorded.

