**Oxytocin/placebo administration + interaction**

After application of the wound, cytokine measurement 1 is performed and TEWL is measured. The test subjects are then given intranasal double-blind placebo or oxytocin (24IU, 3 sprays per nostril; both partners receive either placebo or oxytocin). The positive couple interaction is then explained and practiced. During this exercise, the couples are recorded on video. The first session lasts approximately 2.5 hours (see Figure 1).

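### Section 5.7.3 gives the sub-study 1 wound-healing ANOVAs no couple term; run on 200 people, the oxytocin test exceeds its 5% level if partners' healing is positively correlated

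*Protocol*

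**What the plan says.** - **Allocation.** Section 5.4 randomises couples to four arms: "25 pairs per study arm will be randomly assigned".
- **Treatment.** Under section 5.4.4 the drug is common to the couple: "both partners receive either placebo or oxytocin". Section 5.5.2 also gives the interaction instruction to the couple.
- **Outcome.** Each person contributes a wound, since "both partners receive the suction blisters" (section 5.4.4). The synopsis counts 200 people in 100 pairs, and section 5.4.2 admits heterosexual couples only.
- **Main analysis.** Section 5.7.3 lists the group factors as "oxytocin vs. placebo, men vs. women" and says that the differences "in relation to the main outcome variable wound healing will be evaluated using analyses of variance (ANOVAs". It names no couple factor, couple mean or within-couple term for this comparison. The level is 5%.
- **Partner dependence.** The next sentence of section 5.7.3 uses "hierarchical linear models (HLM) to account for the dependent data structure between partners", but for the associations between the EMA data and wound healing.

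**The concern.** Drug and instruction vary only between couples. Sex varies only within couples, because every couple has one man and one woman. The two kinds of factor need different error terms. An ANOVA on 200 people gives both the same residual, which is right for both only if partners' outcomes are uncorrelated.

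If partners heal alike, two people in a couple carry less information about the drug than two unrelated people, and the drug's standard error comes out too small. For sex the reverse holds: the comparison is made within couples, shared influences cancel, and the standard error comes out too large. The drug test bears on the hypothesis in section 5.2 that oxytocin speeds wound healing, so the stated 5% level of the main efficacy comparison is at stake.

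**Working it through.** **Inputs**
- 100 couples, 25 in each of four arms, hence 50 couples (100 people) per drug (synopsis; section 5.4).
- Level 5% (section 5.7.3), taken as a two-sided test, as the F test is.
- f = .40, power .82, N = 76, raised to 100 for dropouts (section 5.4.1).
- Partner correlation ρ (the ICC): not given. Assumed range 0.1 to 0.5, with 0 and −0.1 as checks.

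**1. The plan's own figure.** For an ANOVA with four groups the noncentrality is λ = f²N = 0.16 × 76 = 12.16 on 3 and 72 degrees of freedom. Power is 0.823, and 76 is the smallest N that reaches .82. The figure reproduces. A single two-level factor does not fit: power would be 0.93 at 76, and 54 would suffice. Section 5.4.1 does not state the unit of N, but the final 100 equals the number of couples. With 100 couples the four-group test at f = .40 has power 0.924 (λ = 16).

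**2. True variances.** Let σ² be the variance between people within a cell.
- Drug: a couple mean has variance σ²(1+ρ)/2, so the difference between two sets of 50 couples has variance 2 × σ²(1+ρ)/(2 × 50) = (σ²/50)(1+ρ).
- Sex: a within-couple difference has variance 2σ²(1−ρ), so the mean over 100 couples has variance 2σ²(1−ρ)/100 = (σ²/50)(1−ρ).
- An ANOVA on people uses 2σ²/100 = σ²/50 for both.

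The assumed variance is therefore wrong by the factor 1+ρ for drug and 1−ρ for sex.

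**3. True level of the nominal 5% test.** Drug: 2[1 − Φ(1.96/√(1+ρ))]. Sex: 2[1 − Φ(1.96/√(1−ρ))]. For example, at ρ = 0.3 the drug test gives 1.96/√1.3 = 1.719 and a two-sided tail of 8.56%.

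**4. Check by simulation.** 40,000 null trials per ρ, 100 couples, eight cells (four arms by sex), 192 error degrees of freedom. The last two columns analyse couple means for drug and within-couple differences for sex, with 96 error degrees of freedom.

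| ρ | Drug, formula | Drug, simulated | Sex, formula | Sex, simulated | Drug, by couple | Sex, by couple |
|---|---|---|---|---|---|---|
| −0.1 | 3.88% | 3.87% | 6.17% | 6.15% | 4.95% | 4.95% |
| 0 | 5.00% | 4.98% | 5.00% | 5.10% | 4.98% | 5.08% |
| 0.1 | 6.17% | 6.14% | 3.88% | 3.88% | 4.98% | 5.00% |
| 0.2 | 7.36% | 7.30% | 2.84% | 3.03% | 5.02% | 5.10% |
| 0.3 | 8.56% | 8.56% | 1.91% | 1.90% | 4.95% | 4.84% |
| 0.5 | 10.95% | 10.82% | 0.56% | 0.57% | 5.05% | 4.85% |

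A four-arm overall test on 200 people, the kind that reproduces the sample size, would run at 6.73%, 8.68%, 11.05% and 15.57% for ρ = 0.1, 0.2, 0.3 and 0.5 (simulated).

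**The case against.** Section 5.7.3 never says that 200 people are treated as independent. An ANOVA with drug between couples and sex within couples is also an ANOVA, and it is valid. Other text points to the couple as the unit: the sample size ends at 100, section 5.7.3 counts completion in couples, the synopsis lists hierarchical models without restricting them to the EMA data, and the reference list includes texts on dyadic data and on hierarchical models. Sub-study 2 does mention repeated measures (section 6.6.2). That contrast is weak, because sub-study 1 also measures its wound outcomes repeatedly (section 5.7.2) and still says only ANOVA. Error terms are, besides, often left to a statistical analysis plan.

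Part of this stands. A reader might infer that the protocol expressly prescribes an analysis that ignores couples; it does not. An analysis on people is the plain reading, not an explicit statement. But this is more than absent detail: the protocol chooses the main-outcome method, lists sex as a group factor beside drug, and places the remedy for partner dependence on a different analysis. An analysis plan that followed it faithfully would carry the problem forward.

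A reader might also infer that the oxytocin test certainly exceeds 5%. The protocol gives no partner correlation for wound healing, and its remark on dependence concerns the EMA associations. The excess is nil at zero correlation and reverses if the correlation is negative. Nor does the sex test deserve equal weight, since section 5.2 states no sex hypothesis for sub-study 1.

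**Conclusion.** The concern holds conditionally. If section 5.7.3 is carried out as it reads, on 200 people, and partners' healing is positively correlated, the nominal 5% oxytocin test is anti-conservative: about 6.2%, 7.4%, 8.6% and 11.0% at ICC 0.1, 0.2, 0.3 and 0.5. The secondary men-versus-women test is conservative: about 3.9%, 2.8%, 1.9% and 0.6%. These sizes rest on the assumed ICC and on both partners of all 100 couples being analysed.

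A positive correlation is plausible, since partners live together and share drug and instruction, but the documents do not establish it. The case for correction does not depend on its value: an analysis by couple held about 5% at every value tried.

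The documents do not support a further inference that the sample size is wrong. Both 76 and 100 fit an analysis by couple.

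**What to change.** In section 5.7.3, state that the couple is the unit of randomisation and inference. Specify a linear mixed model for the wound-healing comparisons, with a couple random effect or an unstructured covariance between the two partners, drug and instruction as between-couple factors, and sex as a within-couple factor.

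Couple means (for drug and instruction) and within-couple differences (for sex) are equivalent only for couples with data from both partners. The compliance rule in section 5.6.1 excludes individuals, so some couples may be left with one partner. The mixed model can keep them, which makes it the better default.

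The cost is a sentence or two. It needs no new data and no change in sample size, and the model belongs to a class the protocol already plans for the EMA associations. If a statistical analysis plan exists and already specifies such a model, section 5.7.3 should be brought into line with it.
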